## Abstract

**Background:**

Coronary artery disease is the leading cause of morbidity and mortality in patients with type 2 diabetes. Screening for asymptomatic coronary artery disease with treatment by means of revascularization seems to be an appealing option for prevention. The utility of such a strategy has never been challenged in a randomized trial.

**Methods/Design:**

In the present study a cohort of diabetic patients without any symptoms and without known coronary artery disease will be screened at two diabetes outpatients services. Those with intermediate or high risk (equal or greater than 10% according to the Italian risk chart) will be asked to participate and enrolled. They will be seen and followed in order to provide the best adherence to medical therapy. Half of the patients will be randomized to undergo an exercise tolerance testing while the other group will continue to be regularly seen at diabetes outpatients services. Best medical/behavioral therapy will be offered to both groups. Those patients with a positive exercise tolerance testing will be studied by coronary angiography and treated according to the severity of coronary lesions by percutaneous stenting or surgery.

The objective of the study is to evaluate the efficacy of the screening strategy aimed at revascularization. A cost-effectiveness analysis will be performed at the end of the follow up.

**Discussion:**

The study will provide useful information about prevention and treatment of diabetic patients at high risk of coronary events. It will be made clearer if detection of silent coronary artery disease has to be recommended and followed by treatment. Given the simplicity of the study protocol, it will be easily transferable to the *real world*.

**Trial registration:**

(ClinicalTrials.gov): NCT00547872

## Background

The association between diabetes and cardiovascular disease is well established. Prevalence of cardiac ischemic disease in the general population is between 2 and 4%, while it reaches 55% among adult diabetic patients [1].

Coronary artery disease is the leading cause of death in diabetic patients accounting for more than 70% of the deaths [2,3].

It is well known that patients with type 2 diabetes without prior myocardial infarction have a similar risk of death from coronary artery disease as patients without diabetes with prior myocardial infarction. Diabetes is considered to be a *risk equivalent *of coronary artery disease for future myocardial infarction and cardiovascular death [4].

Given these strong associations, there is clear need to identify patients with type 2 diabetes who are at risk of cardiovascular events before the onset of symptoms, providing that an effective treatment is available [5].

Observational studies reported a higher rate of acute coronary syndromes in diabetic patients with documented but asymptomatic ischemic coronary artery disease [6]. Nevertheless the hypothesis that revascularization will reduce this risk has never been challenged in a randomized trial.

Screening for coronary artery disease in asymptomatic diabetic patients is thus an appealing but still unexplored concept [7].

According to these observations a screening test should be aimed at detection of severe blockages of the coronary arteries that might warrant treatment.

An ideal test suitable for screening should be safe, sensitive, cheap, repeatable and widely available [8]. Exercise tolerance testing seems close to these ideal characteristics although its sensitivity is low compared with new diagnostic tools available today. On the other hand it does not deliver radiations, it is cheap and really widely available [9].

Recommendations about the use of exercise testing as a screening tool are vague because no clear evidence exists. The American College of Cardiology acknowledges the possible value of exercise testing in people with diabetes who are contemplating an exercise program with a strength of recommendation IIa [10]. The American Diabetes Association suggests exercise testing to diabetic patients when two other major cardiovascular risk factors are present (strength of recommendation IIb) [11]. What to do in case of a positive test it is not known.

U.S. Preventive Task Force states that an "adequately powered randomized trial of screening exercise tolerance testing compared with management based on traditional risk factors would *greatly *inform clinical decision making" [12].

## Method/Design

### General objective

The aim of the study is to evaluate efficacy of screening and treatment of asymptomatic coronary disease in diabetic patients at high risk. Screening is achieved by exercise tolerance testing aimed at revascularization, surgical or percutaneous.

### Primary objective

To assess the effectiveness of screening and treatment of coronary artery disease on the occurrence of cardiac events (acute coronary syndromes or cardiac death) in a group of patients with type 2 diabetes considered at intermediate/high risk according to the risk chart.

### Secondary objective

We will also consider and analyse the impact of screening and treatment of coronary artery disease on the occurrence of symptomatic heart failure. Actually diabetic patients run a higher risk of developing symptomatic heart failure especially after an acute coronary syndrome [13].

### Study Design

The aim of the study is to assess whether screening and treatment of asymptomatic coronary artery disease reduces risk of cardiac events and cardiac death. A prospective *open-label *randomized controlled trial comparing a strategy based on exercise testing aimed at revascularization with management based on pharmacological/behavioural treatment of traditional risk factors has been adopted.

Eligible patients will be randomly assigned (ratio 1:1) to undergo exercise tolerance testing or to continue to be followed by our diabetes outpatients services. Best medical/behavioral therapy will be offered to both groups. Those patients with a positive exercise tolerance testing will be studied by coronary angiography and treated according to the severity of coronary lesions by percutaneous stenting or surgery (Figure 1).

**Figure 1 F1:**
[figure not shown]
**DADDY-D Trial Flow Chart**.

### Study population

Male and female subjects aged ≥ 50 and < 70 years will be eligible for the study if they meet the following inclusion criteria:

#### Inclusion Criteria

• Clinical diagnosis of type 2 diabetes lasting more than one year, based on standard diagnostic criteria (patients on treatment with oral hypoglycaemic agents or insulin or with fasting plasma glucose > 126 mg/dl on two occasions) irrespective of diabetes treatment

• Cardiovascular risk equal or higher than 10% according to the Italian risk chart available on Progetto Cuore website [14,15]

• Ability to exercise and willingness to comply with all study requirements

#### Exclusion Criteria

• Typical symptoms or known coronary artery disease

• Known or symptomatic heart failure

• Exercise testing or any other stress testing performed in the last year before the enrolment

• Electrocardiogram showing left bundle brunch block or ST depression greater than 1 mm at baseline

• Contraindications to double antiplatelet agents treatment (history of aspirin allergy, bleeding tendency, gastrointestinal haemorrhage or peptic ulcers within the last six months, use of anticoagulant therapy, thrombocytopenia)

• Chronic use of non-steroideal anti-inflammatory drugs or steroids

• Glomerular filtration rate less than 40 ml/min/1.73m2 according to MDRD formula [16]

• Presence of any life -threatening condition

• History of active substance or alcohol abuse within the last year or major psychiatric disorder

### Participating Centres

Eligible patients will be screened and recruited by two Diabetes outpatients services of Azienda USL di Modena (located in Modena and Sassuolo).

All of the exercise tolerance testing will be performed at Nuovo Ospedale Civile Sant'Agostino Estense - Medicina Cardiovascolare (Modena), results and ECG traces will be revised by three cardiologists ([name]).

Coronary angiographies will be performed at local reference cardiac catheterization laboratory located in Nuovo Ospedale Civile Sant'Agostino Estense di Baggiovara by four expert cardiologists ([name]). This is a high volume procedure laboratory serving as the hub in our district.

### Participant enrolment

All eligible patients will be asked to participate. Once informed, they will be requested to sign a consent form. At the first visit they will be given a brochure containing detailed information about diabetes, hypertension, atherosclerosis and prevention. All participants will continue with regular follow ups scheduled by the referral diabetes outpatients service.

All smokers will be invited to quit. Physical activity and diet will be encouraged.

At the time of first visit a set of data will be collected:

Personal and clinical data regarding diabetes, cardiovascular risk factors, medications and blood pressure measurements will be collected. Information on laboratory parameters including lipid profile, serum creatinine, HbA1c will also be collected. Cardiovascular risk will be calculated according to the Italian risk chart provided by Istituto Superiore di Sanità [14].

All this data will be abstracted, reported in ad hoc forms and centrally collected.

During follow up the occurrence of any clinical event included in the end-points will be notified and verified through the registers of local Hospital admissions. After the completion of follow each patient will be contacted for the final visit.

### Randomization

Allocation to screening will be separately determined and communicated back by e-mail to diabetes services which will contact patients to schedule exercise testing a few days after their enrolment.

We chose a stratified block randomization with one to one allocation ratio. The allocation sequence was generated through a specific software available on the web [17], the scheme has been kept concealed.

Patients will be stratified according to age (≥ or < 60 years old); gender and cardiovascular risk score (≥ or < 20%).

### Pharmacological/Behavioural prevention of cardiovascular events

Pharmacological/behavioural prevention of cardiovascular events will be the same in both groups. Experimental and control group will continue to be followed at our local Diabetic Clinics that will try to provide maximal adherence the European Society of Cardiology Guideline [18] indications about control of hypertension, hypercholesterolemia and glycaemia.

### Screening procedures

Patients chosen for screening will be scheduled for exercise testing a few days after their enrolment.

A maximal symptom-limited exercise protocol will be used with a treadmill (*T*-*2100 Treadmill *- *GE Healthcare medical system*) according to the standard Bruce protocol. The test will be performed following the American Heart Association Guideline [10]. Twelve ECG leads will be recorded every minute and blood pressure will be measured manually at rest and every three minutes. Ventilatory oxygen consumption, expressed in multiples of resting requirements (METS), will be estimated by exercise duration.

The exercise test will be defined as maximal if the patient will reach 80% of the predicted exercise capacity according to Gulati formula [19]. Sub maximal tests without ECG signs and/or symptoms of ischemia will be considered not diagnostic and will not lead to any other procedure.

The exercise test will be considered positive if showing horizontal or downsloping ST segment depression of 1 mm or more calculated at 0.06-0.08 second after the J point at precordial leads (V3-V6).

Coronary angiography will be proposed to all patients with positive exercise testing.

Coronary angiography will be carried out within 30 days after the exercise testing. All angiography will be performed at our local reference cath-laboratory.

Coronary artery disease will be defined as being significant if lumen stenosis will be greater than 50% at level of left main or left anterior descending, or greater than 70% at level of circumflex or right coronary artery.

Treatment will be decided together with two consultant cardiologists after reviewing coronary anatomy. Treatment (surgery or stenting) will be determined keeping the European Guideline as a reference guide [18].

### Sample Size Estimation

The sample size estimates are based on the following assumptions:

• *Follow up for three years*

• *Event rate in screened population: *1.03/year

Based on existing data we can assume that about 80% patients will test negative [20] and run a risk of 0.97% per year [21] while the remaining 20% of patients will test positive running a risk of 1.03% per year after treatment according to the results of the ACIP trial [22]. This results in a mean risk of 1.03 per year within the group.

• *Event rate in follow up population: *2.6/year

The cardiac event rate reported in over 10000 Italian diabetic patients without evidence of cardiac disease was collected by the Italian Istituto Superiore di Sanità (Diabetes and Informatics Study Group): the cumulative incidence of cardiac events was 2.88% per year in men and 2.33% per year in women [23].

• *Two-sided tests of significance at an alpha = 0.05*

• *Power analysis of 0.80*

Given these assumptions, the total number of subjects to be enrolled is of 364 patients for each arm [24].

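### The screened-arm mean of 1.03% per year does not follow from its stated components, which average 0.98%; at least one printed figure needs correcting

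*Protocol article*

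**What the plan says.** The Sample Size Estimation section of the protocol article lists a screened-arm event rate of 1.03 per year and derives it from two subgroups. About 80% of patients are expected to test negative, at 0.97% per year; "the remaining 20% of patients will test positive running a risk of 1.03% per year after treatment". The derivation closes with "This results in a mean risk of 1.03 per year within the group".

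The control-arm rate is listed as 2.6 per year, supported by a source in which "the cumulative incidence of cardiac events was 2.88% per year in men and 2.33% per year in women". The other inputs are "Follow up for three years", "Two-sided tests of significance at an alpha = 0.05" and "Power analysis of 0.80". The section concludes that "the total number of subjects to be enrolled is of 364 patients for each arm". It cites a reference for the calculation but names no formula, and it does not say how annual rates became 3-year risks.

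The per cent sign is missing after 1.03 and 2.6 in the list of assumptions. I read both as per cent per year, as the surrounding text requires.

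**The concern.** The value 1.03 appears twice: as the rate in the 20% who test positive and as the mean of the whole arm. A weighted mean of two different rates lies strictly between them. It cannot equal the higher rate when most of the weight is on the lower one. Rounding does not explain the gap, and neither does the looseness of the 80% figure.

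The mean is the listed planning rate for the screened arm, so it is one of the two rates behind the sample size. A reader who tries to rebuild the calculation from the components gets a different rate from the one listed. There is a second reason to resolve it: if 1.03 was copied by mistake into the treated-positive line, the protocol misreports its own assumption about outcome after revascularization, which is part of the strategy under test.

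**Working it through.** **Inputs** (Sample Size Estimation, except the 1:1 allocation, which is in Study Design): negatives 80% at 0.97% per year; treated positives 20% at 1.03% per year; stated screened-arm mean 1.03% per year; control rate 2.6% per year (the simple mean of 2.88 and 2.33 is 2.605); 3 years; two-sided alpha 0.05; power 0.80; 364 per arm.

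**Step 1: the mean.** 0.80 x 0.97 + 0.20 x 1.03 = 0.776 + 0.206 = 0.982% per year. The stated mean is 1.03%, which is 0.048 percentage points higher.

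**Step 2: what would make 1.03% true.** Change one component at a time:

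- Treated-positive rate: (1.03 - 0.776) / 0.20 = 1.27% per year, which is 23% above the printed 1.03%.
- Negative rate: (1.03 - 0.206) / 0.80 = 1.03% per year, so both subgroups would have the same risk.
- Split: the mean reaches 1.03% only if every patient tests positive.

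Of these, only the first leaves two subgroups with different risks.

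**Step 3: the plan's own sample size.** The formula is not stated, so I assume the usual pooled two-proportion one, without continuity correction:

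n per arm = [1.96 x sqrt(2 x p x (1 - p)) + 0.8416 x sqrt(p1(1 - p1) + p2(1 - p2))]^2 / (p1 - p2)^2, with p = (p1 + p2) / 2.

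Taking 3-year risk as 3 x the annual rate, p1 = 0.0309, p2 = 0.0780 and p = 0.05445. The two square roots are 0.3209 and 0.3192, and n = 363.1, so 364 per arm. This matches the stated figure.

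**Step 4: the same formula with the other rates and the other conversion.** Exponential conversion is 1 - exp(-3 x annual rate), which gives a control risk of 0.0750.

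| Screened-arm rate | Conversion | 3-year risks | n per arm | Power at 364 |
|---|---|---|---|---|
| 1.03% | 3 x annual | 3.09% vs 7.80% | 363.1, so 364 | 0.80 |
| 0.982% | 3 x annual | 2.95% vs 7.80% | 337.6, so 338 | 0.83 |
| 1.03% | exponential | 3.04% vs 7.50% | 392.9, so 393 | 0.77 |
| 0.982% | exponential | 2.90% vs 7.50% | 364.7, so 365 | 0.80 |
| 0.98% | exponential | 2.90% vs 7.50% | 363.5, so 364 | 0.80 |

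The stated 364 is therefore reproduced exactly in two ways: from 1.03% with 3 x the annual rate, and from 0.98%, the correctly computed mean after rounding, with exponential conversion.

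**Step 5: effect on expected events.** Over three years in 364 screened patients, 364 x 0.0309 = 11.2 events against 364 x 0.02946 = 10.7, a difference of about 0.5.

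**The case against.** The strongest reply is that this is a slip in the text with no practical consequence. It may be a single misprinted component, with the planning rate and the sample size intact. Alternatively, 364 may already have been computed from 0.98% with exponential conversion, in which case only the printed mean is wrong. Even if 0.98% is right and 3-year risk was taken as 3 x the annual rate, the error is conservative: 364 exceeds the 338 required. The gap of about 0.05 percentage points is small beside an assumed difference of about 1.6 (2.6 - 1.03 = 1.57).

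Most of this stands, and it rules out three stronger readings that a reader might infer:

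- **That the planning rate of 1.03% is itself wrong.** The documents show only that the figures conflict. The cited sources are not available here, and 1.27% in treated positives would leave 1.03% correct.
- **That the trial needs 338 per arm and is oversized.** This holds under one conversion only. The protocol does not state its conversion, and the exponential one returns 364 from the correct mean.
- **That the yearly interim check would use a misleading benchmark.** The Interim Analyses section refers to verifying the event-rate assumption but sets no numerical threshold, and half an event over three years would not be detectable.

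What the reply does not do is make the sentence true. Under every reading, at least one printed figure is wrong.

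**Conclusion.** The inconsistency is certain and needs no outside source: the printed components average 0.982% per year, and the listed mean is 1.03%. Which figure is wrong cannot be settled from the protocol article.

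The consequence for sample size is modest and depends on the case. If a component is misprinted and 1.03% is right, 364 is unaffected under 3 x the annual rate. If the mean is 0.98%, 364 gives power of about 0.83 under 3 x the annual rate and 0.80 under exponential conversion. The only unfavourable combination is 1.03% with exponential conversion (393 per arm, power 0.77 at 364). Nothing in the text shows that this was used, and it does not reproduce the stated number.

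These figures assume the pooled two-proportion formula, a control rate of 2.6% per year and no allowance for loss to follow-up. This is a minor but real correction to a planning input, not a flaw in the design.

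**What to change.** 1. Check the cited sources and the original calculation to find which figure is wrong.
2. Correct that figure: either restate the screened-arm mean as 0.98% per year, or correct the component (for example, 1.27% per year in treated positives would give 1.03%).
3. State the formula and how annual rates were converted to 3-year risk.
4. Restate N or power to match the reconciled rate and the conversion actually used. Do not print 338 unless the calculation is confirmed to have used 3 x the annual rate.
5. Add the missing per cent signs to the two listed event rates.

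The cost is a corrected figure and a sentence or two in the sample-size section. Enrolment need not change.

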## Discussion

The study will be among the first randomised trials to investigate the effectiveness and cost-utility of a strategy of screening for unknown coronary artery disease in diabetic patients aimed at revascularisation. Recently the publication of DIAD trial results [27] demonstrates that screening asymptomatic diabetic patients by myocardial perfusion imaging without any treatment strategy does not affect outcome. This study cannot be considered the last word in this field because a screening plan should be performed only if treatment is available when positive cases are found. DIAD study design is not thought to test screening and treatment together but screening alone. Moreover the screening tool was myocardial perfusion imaging, a very sensitive and specific test, but with considerable radiation burden. In case of favourable results such a strategy would not be applicable to a large population due to costs and risks. Exercise tolerance testing is a simple and cheap test with low or no risk, it does not deliver radiations. In case of positive results the same strategy would be completely feasible in the *real world*.

Even the publication of BARI 2D [28] trial results does not represent the final answer to the dispute. BARI 2D was not designed as screening trial, patients with left main disease were excluded and patients with history of heart failure or ischemic heart disease were included. Furthermore a benefit in terms of major cardiovascular events was observed in patients undergone coronary artery bypass.

This study is designed as screening and treatment study and mandate coronary angiography for every patient with positive exercise testing. In case of coronary blockages, revascularization (percutaneous or surgical) is proposed. The results will help to establish if a screening strategy followed by revascularization is the best approach to high risk diabetic patients.

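### The 0.80 power at 364 per arm is a best case: it assumes that every screened patient is negative or a treated positive and that nobody is lost, which the trial's own procedures do not secure

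*Protocol article*

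**What the plan says.** The Sample Size Estimation section of the protocol article lists "Follow up for three years", "Two-sided tests of significance at an alpha = 0.05" and "Power analysis of 0.80". It takes 2.6% per year for the control arm. For the screened arm it takes 80% negatives at 0.97% per year and gives the remaining 20%, all positives, a post-treatment rate of 1.03%. It then says: "This results in a mean risk of 1.03 per year within the group". The result is that "the total number of subjects to be enrolled is of 364 patients for each arm".

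The Screening procedures section describes a different flow. "Sub maximal tests without ECG signs and/or symptoms of ischemia will be considered not diagnostic and will not lead to any other procedure". For positives, "Coronary angiography will be proposed to all patients with positive exercise testing". The Discussion, however, says that the study will "mandate coronary angiography for every patient with positive exercise testing".

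The Statistical analysis section sets intention to treat. The Interim Analyses section provides yearly checks of the sample-size assumptions on the primary event rate, which may influence the length of follow-up.

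**The concern.** The sample-size model has two classes of screened patient, and the procedures create at least two more: patients whose test is not diagnostic and who go no further, and positives who decline the proposed angiography. Under intention to treat both stay in the screened arm. If their risk is above the modelled rates, the screened-arm rate moves towards control and the contrast shrinks. Patients with no usable outcome reduce the effective number as well.

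The stated figure leaves no room for any of this. A reader who takes 0.80 as the power of the planned comparison would be relying on full diagnostic yield, full uptake and complete follow-up, and a null result would be harder to interpret than the stated power suggests.

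**Working it through.** **Inputs from Sample Size Estimation.** Two-sided alpha 0.05; power 0.80; 3 years; screened arm 1.03% per year; control arm 2.6% per year. Allocation is 1:1 (Study Design). Annual rates are multiplied by 3: p1 = 0.0309, p2 = 0.078, mean p = 0.05445.

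**Reproducing 364.** Pooled two-proportion formula without continuity correction:

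n = [1.96·√(2p(1−p)) + 0.8416·√(p1(1−p1) + p2(1−p2))]² / (p1−p2)²
= (0.6289 + 0.2686)² / 0.002218 = 363.1, rounded up to 364.

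Power at n = 364 is Φ{[√n·|p1−p2| − 1.96·√(2p(1−p))] / √(p1(1−p1) + p2(1−p2))} = Φ{(0.8986 − 0.6289)/0.3192} = 0.801. The match is exact with zero loss, so no allowance is hidden in the number.

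**The weighted mean.** 0.8 × 0.97 + 0.2 × 1.03 = 0.776 + 0.206 = 0.982% per year, not 1.03%. (A mean of 1.03% would need positives at (1.03 − 0.776)/0.2 = 1.27%.) At 0.982% the same formula needs 338 per arm, and 364 gives 0.829. Both baselines are carried below and kept apart.

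**Departures.** The article gives none of the shares, so these are assumptions. With baseline b (% per year):

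- Loss d: n = 364 × (1 − d), rates unchanged.
- Non-diagnostic share x at rate k: (1 − x)·b + x·k, with k = 1.8% (an assumed intermediate value) or 2.6% (the control rate).
- Share y of positives untreated at rate u: b + 0.2·y·(u − 1.03). Here u is 2.6%, or the value implied if the control arm has the same 80/20 mix and negatives keep 0.97%: (2.6 − 0.776)/0.2 = 9.12%.
- Joint: (1 − x)·[b + 0.2·y·(u − 1.03)] + x·k, with n = 364 × (1 − d).

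| Assumed departure | Rate from 1.03% | Power | Rate from 0.982% | Power |
|---|---|---|---|---|
| None | 1.030 | 0.801 | 0.982 | 0.829 |
| 5% lost | 1.030 | 0.780 | 0.982 | 0.809 |
| 10% lost | 1.030 | 0.758 | 0.982 | 0.788 |
| 5% non-diagnostic at 1.8% | 1.069 | 0.777 | 1.023 | 0.805 |
| 10% non-diagnostic at 1.8% | 1.107 | 0.752 | 1.064 | 0.780 |
| 10% non-diagnostic at 2.6% | 1.187 | 0.696 | 1.144 | 0.727 |
| 10% of positives untreated at 2.6% | 1.061 | 0.782 | 1.013 | 0.811 |
| 10% of positives untreated at 9.12% | 1.192 | 0.692 | 1.144 | 0.727 |
| 5% of each; k = 1.8%, u = 2.6% | 1.083 | 0.746 | 1.038 | 0.776 |
| 5% of each; k = 1.8%, u = 9.12% | 1.145 | 0.703 | 1.100 | 0.735 |
| 5% of each; k = 2.6%, u = 9.12% | 1.185 | 0.675 | 1.140 | 0.707 |

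Example, last row from 1.03%: 1.03 + 0.2 × 0.05 × 8.09 = 1.1109; 0.95 × 1.1109 + 0.05 × 2.6 = 1.185; n = 364 × 0.95 = 345.8; power 0.675.

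**Does the formula matter?** The planned test is the log-rank. With constant hazards and the 1.03% rate, the Schoenfeld approximation gives 0.818 with no departure, 0.798 at 5% loss and 0.761 with 5% non-diagnostic at 2.6%. Freedman's gives 0.764 with no departure. The pattern is the same: little or no slack.

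**The case against.** The strongest reply is that there is no error in 364 itself: on its stated inputs it delivers 0.801. That stands. A reader might infer that 364 simply fails to deliver 0.80, or that the shortfall is large; the article supports neither. The shares are unknown, and so are the risks of the affected patients. Non-diagnostic tests are by definition those without signs of ischemia, so the control rate may be too pessimistic for them. The 9.12% is back-solved and appears nowhere in the article. The true weighted mean, 0.982%, also gives a small cushion that survives 5% loss (0.809) or 5% non-diagnostic at 1.8% (0.805).

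The eligibility criteria help as well. They require ability to exercise and willingness to comply, and events are verified through hospital admission registers. This should limit the shares but does not remove them, since the procedures expressly provide for non-diagnostic tests.

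A reader might also infer that any shortfall would surface only at the end. The Interim Analyses section contradicts that, and longer follow-up could restore power: with 10% non-diagnostic at 2.6% per year, the formula gives 0.696 at three years and 0.823 at an assumed four (4.748% against 10.4%). But the section gives no rule for this, the Timing section dates the final analysis on three-year data, and the check concerns event rates. Dilution raises the screened-arm rate, so a pooled rate would show more events and would not reveal the smaller contrast.

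It is also tempting to add that positives without significant stenosis dilute the effect. Nothing in the article shows that they carry excess risk, so that does not stand.

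Finally, an article condenses a fuller protocol. That would excuse a missing detail, but here the stated number demonstrably contains no allowance, and its two-class model conflicts with the procedures in the same article. The difference between proposing and mandating angiography may be loose wording, since a required offer can be declined; it changes no figure in the calculation but does bear on the uptake that the calculation assumes.

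**Conclusion.** The concern holds in a limited form. The 364 per arm is exactly the zero-loss, full-uptake number, so the stated 0.80 is a best case and not the expected power of the intention-to-treat comparison under the described procedures. From the stated 1.03%, every departure examined takes power below 0.80. From the correct 0.982%, 5% loss, 5% non-diagnostic at 1.8%, or 10% of positives untreated at 2.6% is absorbed. The other single departures in the table are not, and neither is 5% of each together under any of the risks tried (0.707 to 0.776). All of these sizes rest on assumed shares and on assumed risks for the affected patients, so they show sensitivity and are not a forecast.

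**What to change.** Keep 364 per arm. In Sample Size Estimation, correct the weighted mean to 0.982% (or correct the component rates if 1.03% is what was meant), and restate power as a range with explicit shares for non-diagnostic tests, declined angiography and loss to follow-up. Recruitment began in September 2007 according to the Timing section, so the first two shares can be taken from the exercise tests already done. Let the yearly checks in Interim Analyses also compare the observed shares with those assumed. Reconcile the statements on angiography in Screening procedures and in the Discussion. The cost is a recalculation and probably a less favourable stated power, with no extra patients.

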### Statistical analysis

The results will be evaluated based on the intention to treat analysis.

The incidence rates will be estimated using Kaplan-Meier survival curves that will be compared using logrank analysis. The treatment efficacy will be assessed by multivariate analyses using Cox's regression model.

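### At the printed rates of 1.03% and 2.6% per year, 364 patients per arm give power slightly below the stated 0.80

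*Protocol article*

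**What the plan says.** The Sample Size Estimation section of the protocol article lists its assumptions in turn.

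- Duration: "Follow up for three years".
- Screened arm: it assumes that "about 80% patients will test negative [20] and run a risk of 0.97% per year", and that "the remaining 20% of patients will test positive running a risk of 1.03% per year after treatment". It then states: "This results in a mean risk of 1.03 per year within the group".
- Control arm: 2.6 per year, from a national cohort in which "the cumulative incidence of cardiac events was 2.88% per year in men and 2.33% per year in women".
- Error rates: two-sided alpha 0.05 and "Power analysis of 0.80".
- Result: "the total number of subjects to be enrolled is of 364 patients for each arm".

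The section prints no three-year risks and no formula; it gives a reference for the calculation. The Statistical analysis section plans Kaplan-Meier curves "compared using logrank analysis", followed by a Cox model. Allocation is 1:1 (Study Design).

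**The concern.** The primary outcome is the occurrence of a cardiac event, analysed as time to event. A patient who has had a first event is no longer at risk of one, so three years at a given annual rate produce a cumulative risk somewhat below three times that rate. The gap is larger in the arm with the higher rate, so tripling widens the planned difference and makes the required sample size look smaller.

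If that was done, the stated power would not be reached even if every planning assumption were true and no patient were lost. It would also matter for the yearly interim checks, which compare observed event rates with the planning assumptions and can alter the length of follow-up. A tripled control risk of 7.80% is a slightly wrong yardstick for a Kaplan-Meier estimate when the stated rate implies 7.50% to 7.60%.

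**Working it through.** **Inputs, all from the protocol article.** Screened rate r1 = 1.03% per year, control rate r2 = 2.6% per year, T = 3 years, two-sided alpha 0.05 (z = 1.960), power 0.80 (z = 0.8416), 1:1 allocation, 364 per arm. The two arm rates are printed without a percent sign; their components carry one, so percentages are meant.

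**Formula.** Two proportions, pooled variance, no continuity correction:

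n = [1.960·√(2·p̄(1−p̄)) + 0.8416·√(p1(1−p1) + p2(1−p2))]² / (p2−p1)²

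**Step 1: reproduce 364.** Tripled rates are p1 = 3.09% and p2 = 7.80%, a difference of 4.71 points, with p̄ = 5.445%.

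n = (0.6289 + 0.2686)² / 0.0471² = 363.1, so 364 per arm, with power 0.801.

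At the same tripled risks, other common methods give different answers: unpooled 361, continuity-corrected 405, arcsine 347, Schoenfeld about 321 to 340, Freedman about 377 to 386.

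**Step 2: convert the same rates to three-year risks.** Power at 364 is Φ{[(p2−p1)·√364 − 1.960·√(2·p̄(1−p̄))] / √(p1(1−p1) + p2(1−p2))}.

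| Reading of the annual figures | Three-year risks | Difference | n per arm for 0.80 | Power at 364 |
|---|---|---|---|---|
| Tripled | 3.09% v 7.80% | 4.71 | 364 | 0.801 |
| Yearly risks, 1−(1−r)³ | 3.06% v 7.60% | 4.54 | 383 | 0.780 |
| Constant rates, 1−exp(−3r) | 3.04% v 7.50% | 4.46 | 393 | 0.769 |

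The formula therefore asks for 383 − 364 = 19 or 393 − 364 = 29 more patients per arm, which is 5% or 8%.

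**Step 3: the planned test.** Log-rank test simulated with 364 per arm, exponential event times, all patients followed for exactly three years and none lost (40,000 runs each): power 0.783 with constant rates of 1.03% and 2.6%, and 0.791 if these are yearly risks. Approximations over the same two readings: Freedman 0.764 to 0.775, exponential-rate (Lachin) formula 0.766 to 0.776, Poisson rate comparison 0.777 to 0.788, Schoenfeld 0.818 to 0.829.

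**Step 4: the other route to 364.** The components printed in the section give 0.8 × 0.97 + 0.2 × 1.03 = 0.776 + 0.206 = 0.982% per year, not 1.03%. With exponential conversion against 2.6%:

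- 0.98% gives n = 363.5, so 364 per arm.
- 0.982% gives n = 364.7, so 365 per arm, with power 0.799 at 364. Simulated log-rank power is about 0.81.

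Two routes therefore lead to 364: the printed 1.03% with tripling, or the component mean with correct conversion.

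**The case against.** Four points can be made for the plan.

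- **The mechanism is not documented.** A reader might infer that the authors certainly tripled the rates. The article does not show this: it prints no formula, and the component mean of 0.98% with exponential conversion also gives 364. This stands, so tripling can only be called the likely explanation. It does not rescue the paragraph, because 1.03 is what is printed as the planning rate. Either that rate or the power is misstated.
- **The planned test is the log-rank test, and the inputs read more like yearly risks than constant rates.** This also stands. On that reading the shortfall is about one point (0.79), and 0.77 belongs to a two-proportion test that the trial does not plan. The Schoenfeld approximation shows no shortfall at all, but the hazard ratio here is about 0.40, and direct simulation of the log-rank test does not support its value.
- **Early enrolees could be followed for longer.** Recruitment is scheduled from September 2007 to December 2009, and the last patient reaches three years in December 2012. If everyone were followed to that date (assuming uniform accrual over 27 months), power would be about 0.89 to 0.90. The sample size section, however, rests on three years of follow-up, and the stated 0.80 has to be judged on that basis.
- **Interim checks may change the follow-up.** They could absorb a discrepancy of this size. That limits the consequence but does not correct the printed figure.

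**Conclusion.** The printed combination of 1.03% and 2.6% per year, three years, two-sided alpha 0.05 and 364 per arm does not deliver power of 0.80. It delivers about 0.78 to 0.79 with the planned log-rank test, or 0.77 to 0.78 by the two-proportion formula. The shortfall is thus 1 to 3 points. If the screened-arm rate was really 0.98%, power is about 0.80 and the error lies in the printed rate.

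These values assume proportional hazards with constant rates, complete follow-up to exactly three years and no losses. Nothing here shows that the trial is materially underpowered or must enrol more patients, although a reader might infer that from the 383 or 393 per arm. It is a minor correction to a headline design figure.

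**What to change.** In the Sample Size Estimation section, print the three-year risks, the conversion used (1−(1−r)³ for yearly risks, 1−exp(−3r) for constant rates) and the sample size formula. Then take whichever branch matches the calculation that was actually done:

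- If 1.03% is the intended screened-arm rate, restate the power of 364 per arm as about 0.78 to 0.79 for the planned log-rank test (0.77 to 0.78 by the two-proportion formula).
- If 0.98% was used, correct the screened-arm rate to 0.98% and keep 0.80.

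Use the same converted risks as the reference for the yearly event-rate checks. The cost is a few reworded lines. Enrolment, procedures and analysis stay as they are; under the first branch the stated power becomes slightly less favourable.
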